## Abstract

**Background:**

Breast cancer (BC) is the most common invasive cancer in women, and exercise can significantly improve the outcomes of BC survivors. MoviS (Movement and Health Beyond Care) is a randomized controlled trial aimed to evaluate the potential health benefits of exercise and proper nutritional habits. This study aims to assess the efficacy of aerobic exercise training in improving quality of life (QoL) and health-related factors in high-risk BC.

**Methods:**

One hundred seventy-two BC survivor women, aged 30–70 years, non-metastatic, stage 0–III, non-physically active, 6–12 months post-surgery, and post chemo- or radiotherapy, will be recruited in this study. Women will be randomly allocated to the intervention arm (lifestyle recommendations and MoviS Training) or control arm (lifestyle recommendations). The MoviS training consists of 12 weeks of aerobic exercise training (2 days/week of supervised and 1 day/week of unsupervised exercise) with a progressive increase in exercise intensity (40–70% of heart rate reserve) and duration (20–60 min). Both arms will receive counseling on healthy lifestyle habits (nutrition and exercise) based on the World Cancer Research Fund International (WCRF) 2018 guidelines.

The primary outcome is the improvement of the QoL. The secondary outcomes are improvement of health-related parameters such as Mediterranean diet adherence, physical activity level, flexibility, muscular fitness, fatigue, cardiorespiratory fitness (estimated maximal oxygen uptake), echocardiographic parameters, heart rate variability (average of the standard deviations of all 5 min normal to normal intervals (ASDNN/5 min) and 24 h very low and low frequency), and metabolic, endocrine, and inflammatory serum biomarkers (glycemia, insulin resistance, progesterone, testosterone, and high-sensitivity C-reactive protein).

**Discussion:**

This trial aims to evaluate if supervised exercise may improve QoL and health-related factors of BC survivors with a high risk of recurrence. Findings from this project could provide knowledge improvement in the field of exercise oncology through the participation of a multidisciplinary team that will provide a coordinated program of cancer care to improve healthcare quality, improve prognosis, increase survival times and QoL, and reduce the risk of BC recurrence.

**Trial registration:**

ClinicalTrials.gov NCT04818359. Retrospectively registered on March 26, 2021

## Administrative information

Note: the numbers in curly brackets in this protocol refer to SPIRIT checklist item numbers. The order of the items has been modified to group similar items (see http://www.equator-network.org/reporting-guidelines/spirit-2013-statement-defining-standard-protocol-items-for-clinical-trials/).

## Introduction

### Background and rationale {6a}

Breast cancer (BC) is the most common invasive cancer in women in all age groups. The number of new cases diagnosed worldwide in 2018 reached 2.1 million, and this value is expected to reach 3.2 million in 2050, with the highest incidence in industrialized countries [1]. While the incidence tends to rise, early diagnosis and more targeted therapies have resulted in a significant increase in the 5-year survival rate [2]. Although this finding is undoubtedly positive, it should nevertheless be emphasized that treatments such as surgery, radiotherapy, axillary emptying, chemotherapy, and hormonal therapy can cause long-term effects such as depression, anxiety, and fatigue that contribute to worsening patients’ quality of life (QoL) [3].

MoviS originates from the hypothesis that the primary treatment for BC is a “critical moment” for changes in lifestyle and the involvement of local cultural associations and no profit organizations particularly careful to the initiatives related to prevention and well-being beyond the cure in the field of oncological diseases, which helped the construction of a cancer survivor network that organizes, behind the project, events such as seminars on lifestyle, discussion boards among the patients and the experts and social support network the involvement of the patient asking for their opinion and contribution helped in shifting towards patient-centered care with the active involvement of patients and public in research design at the beginning and to active participation throughout the research process. This project therefore not only aims to lay the groundwork for the development of a consultancy service on the importance of an active lifestyle for BC patients but also to create an educational program that could be adopted by regional oncology units as part of a broader regional strategy promoting healthy lifestyles and cancer prevention and moving beyond clinical treatment.

Cohort studies conducted on patients in post-treatment follow-up have shown that physical exercise may be particularly suitable in this phase, as it improves psycho-physical and cardiometabolic health in patients who have completed adjuvant therapy [4, 5].

Regular physical activity is able to facilitate the improvement and recovery of autonomy through functional re-education and postural re-equilibrium, promotes socialization, and reduces anxiety and depression [6]. Furthermore, it has recently been reported that aerobic exercise can help to alleviate typical cancer-related fatigue in patients with breast cancer after diagnosis or treatment [7], and that, exercise supervision by an exercise specialist may represent a strength in the achievement and maintenance of physical activity recommendation for cancer survivors [8–10].

Nutritional aspects are also important in cancer post-treatment follow-up, by the modulation of hormonal levels related to cancer progression such as hyperglycemia, abdominal fat, and IGF-1 [11, 12]. It has been shown that the risk of recurrences could be prevented through a proper diet, weight control, and physical activity [13].

Physical exercise and healthy nutrition should be then considered during cancer follow-up, with aims to improve QoL, physiological parameters, and prognosis [14].

The aim of this research project is to evaluate the effects of supervised exercise and lifestyle changes on QoL and health-related factors such as respiratory, cardiac, and muscle function indexes; fatigue; body composition; and psychological well-being in BC survivors with a high risk of recurrence. Moreover, as a marked impairment in metabolic function is associated with more aggressive postmenopausal breast tumor biology [15], parameters such as glycemia and HOMA-IR will be analyzed.

Given the body of literature available on the relationship between lifestyle changes and physio-metabolic improvements and QoL [5–7], we expect to find relationships between circulating molecular markers and functional parameters. In addition, this project could improve knowledge on differences between lifestyle recommendations and supervised exercise and diet counseling.

## Objectives {7}

The main objective of the MoviS project is to evaluate if supervised exercise may improve QoL and health-related factors of BC survivors with a high risk of recurrence. The intervention aims at changing the lifestyle of BC women, evaluated through monitoring physical, functional, psychological, and metabolic parameters.

## Trial design {8}

MoviS is a randomized controlled trial (RCT) on the effect of aerobic exercise training on QoL in BC survivors. Participants will be randomized to undergo either a supervised exercise program and lifestyle recommendations or lifestyle recommendations only. Groups will be divided following a parallel arm design with a 1:1 ratio.

## Methods: participants, interventions, and outcomes

### Study setting {9}

Patients taken in charge by the oncology clinic of the Medical Oncology Unit of the Urbino Hospital (PU, Italy) will be pre-recruited and carefully informed on the modalities through which the project will take place. Patients that meet all the inclusion criteria described below will be recruited and randomized for the intervention phase.

### Eligibility criteria {10}

Patients (women only) will be enrolled following the inclusion criteria:Diagnosis of BC (stage 0 to III, without metastases or recurrence diagnosis at recruitment)After surgery (maximum 12 months) and chemotherapy and/or radiotherapy treatments (minimum 6 months)Risk of recurrence, which was identified if the participants present at least 1 of the following conditions: BMI at diagnosis ≥ 25 kg/m^2^, testosterone ≥ 0.4 ng/mL, serum insulin ≥ 25 μU/mL (170 pmol/L), and metabolic syndrome. Metabolic syndrome was defined as the presence of at least 3 of the following 5 factors: (I) glycemia ≥ 100 mg/dL (6.05 mmol/L), (II) triglycerides ≥150 mg/dL (1.69 mmol/L), (III) HDL-C < 50 mg/dL (1.29 mmol/L), (IV) waist circumference ≥ 80 cm, and (V) blood pressure ≥ 130/85 mmHg.Non-physically active, namely participants must be not regularly active (according to the International Physical Activity Questionnaire Short Form [IPAQ-SF]) [16, 17] for at least 6 months

Exclusion criteria:Not suitable for non-competitive physical activity after the cardiological medical examinationDisabling pneumological, cardiological, neurological, and orthopedic comorbidities and mental illnesses that prevent the exercise performanceTreatment with drugs that alter the heart rate response to exerciseTreatment with antidepressant drugs

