Secondary outcome measure:2.Fatigue: change in fatigue perception assessed by the brief fatigue inventory (BFI) questionnaire. The score of the questionnaire ranges from 0 to 90. A higher score means more severe fatigue.3.Anthropometry: change body mass index (BMI) expressed as kg/m^2^.4.Body composition: change fat mass (%) assessed by bioelectrical impedance analysis.5.Cardiac function indexes: change in the global longitudinal strain (%) assessed by echocardiography.6.Heart rate variability: change in heart rate variability assessed by 24-Holter monitoring.7.Cardiorespiratory fitness: change in cardiorespiratory fitness assessed by estimated maximal oxygen uptake (mL/min/kg).8.Flexibility: change in muscle flexibility assessed by sit and reach test (m).9.Muscular fitness: change strength assessed by isometric hand grip strength test (kg).10.Proprioceptive recalibration: change assessed by stabilometry (mean velocity) (mm^2^/s^2^).11.Posture balance: change assessed by stabilometry (Romberg Quotient test-European variant) (% over or under 100).12.Upper limb muscle viscoelastic characteristics: change in the muscle properties of the pectoralis major, upper trapezius, and sternoclavicular mastoid muscle assessed by a hand-held myotonometer.13.Psychological well-being: change in mood profile assessed by the Profile of Mood States (POMS) questionnaire. The POMS questionnaire gives a 5-point Likert scale; a higher score indicates increased negative mood.14.Homeostatic Model Assessment for Insulin Resistance (HOMA-IR) Index: change in HOMA-IR Index calculated as HOMA-IR = (FPI × FPG)/22.5, where FPI is fasting plasma insulin concentration (mU/L) and FPG is fasting plasma glucose (mmol/L), or as HOMA-IR = (FPI × FPG)/405 if fasting plasma glucose is expressed in mg/dL.15.Insulin-like growth factor (IGF-1): change in IGF-1 assessed by blood samples (μg/L).16.C-reactive protein: change in high sensitivity C-reactive protein assessed by blood samples (mg/L).17.Gut microbiota: change in microbial diversity (species diversity %) assessed by next-generation sequencing (NGS) of the V3–V4 region of the 16S rDNA gene.18.Osteoporosis level: change in computerized bone mineralometry assessed by *T*-score (normal: +2.5> *T*-score > −1.0; osteopenia: −1.0> *T*-score >−2.5; osteoporosis: *T*-score <−2.5; severe osteoporosis: *T*-score <−2.5 with one or more fragility fractures).19.Recurrences: recurrence-free interval defined as the time from registration to the time of documented recurrent disease.

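### The glycaemia factor of metabolic syndrome is printed with two unequal cut-offs, 100 mg/dL and 6.05 mmol/L, and the protocol does not say which governs

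*Protocol article*

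**What the plan says.** In the protocol article, Eligibility criteria {10}, a woman must be at risk of recurrence: "Risk of recurrence, which was identified if the participants present at least 1 of the following conditions". There are four such conditions: BMI at diagnosis, testosterone, serum insulin, and metabolic syndrome. The last is built from components: "Metabolic syndrome was defined as the presence of at least 3 of the following 5 factors". The first of the five factors is "glycemia ≥ 100 mg/dL (6.05 mmol/L"). The two lipid factors follow the same layout, mg/dL first and mmol/L in brackets: "triglycerides ≥150 mg/dL (1.69 mmol/L") and "HDL-C < 50 mg/dL (1.29 mmol/L").

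Outcomes {12}, item 14, defines HOMA-IR in two ways. With glucose in mmol/L it is "HOMA-IR = (FPI × FPG)/22.5". The alternative is "HOMA-IR = (FPI × FPG)/405 if fasting plasma glucose is expressed in mg/dL". The section on eligibility does not state which of the two glycaemia values governs, or in which unit the screening laboratory reports.

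**The concern.** A bracketed SI value should be the same threshold in another unit. Here it is not, so the criterion can be read in two ways. The bracketed value is the stricter one: a woman whose glycaemia falls between the two figures has the factor when it is read in mg/dL and lacks it when it is read in mmol/L.

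The criterion matters because risk of recurrence defines the population named in the trial's main objective. An inclusion threshold should lead to the same decision for every woman screened, and a reader should be able to reproduce it. At stake are the eligibility decisions for a narrow set of women and the accuracy of the published population definition.

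**Working it through.** **Inputs from the document**

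- Glycaemia cut-off: 100 mg/dL, with 6.05 mmol/L in brackets (Eligibility criteria {10}).
- HOMA-IR divisors: 22.5 for glucose in mmol/L, 405 for glucose in mg/dL (Outcomes {12}, item 14).

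**Step 1. The document's own conversion factor.** Both formulas must give the same HOMA-IR for the same woman, with insulin unchanged. Hence glucose(mg/dL)/405 = glucose(mmol/L)/22.5, and the factor is 405/22.5 = 18.0 mg/dL per mmol/L.

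**Step 2. Try to reproduce the printed value.** 100/18.0 = 5.56 mmol/L, not 6.05. To obtain 6.05 from 100 the factor would have to be 100/6.05 = 16.53. The printed pair does not reproduce.

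**Step 3. Convert the bracketed value back.** 6.05 × 18.0 = 108.9 mg/dL.

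**Step 4. Size of the gap.** 108.9 − 100 = 8.9 mg/dL; 6.05 − 5.56 = 0.49 mmol/L; 8.9/100 = 8.9%. Rounding to two decimals cannot produce a gap of this size.

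**Step 5. Sensitivity to the factor.** With the molar-mass factor for glucose, 18.016 (an assumption, not in the document), 100 mg/dL is 5.55 mmol/L and 6.05 mmol/L is 109.0 mg/dL. The result is the same.

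**Step 6. Neighbouring pairs as a control.** The document gives no lipid factors, so these are assumptions: 88.57 for triglycerides and 38.67 for HDL-C.

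| Factor | mg/dL | Printed mmol/L | Recomputed mmol/L |
|---|---|---|---|
| Glycaemia | 100 | 6.05 | 100/18.0 = 5.56 |
| Triglycerides | 150 | 1.69 | 150/88.57 = 1.69 |
| HDL-C | 50 | 1.29 | 50/38.67 = 1.29 |

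The lipid pairs agree and the glycaemia pair does not. The finding itself rests on steps 1 to 3 alone. The insulin pair, 25 μU/mL with 170 pmol/L, implies 170/25 = 6.8 pmol/L per μU/mL. The document gives no factor to test this against, so no conclusion is drawn about it.

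**Step 7. When eligibility changes.** Take glycaemia of 104 mg/dL, which is 104/18 = 5.78 mmol/L. It meets the cut-off of 100 mg/dL and falls short of 6.05 mmol/L. With exactly two other factors, she has three under the first reading (metabolic syndrome) and two under the second (none). With three or four other factors she qualifies either way; with one or none she fails either way. If her BMI, testosterone or insulin reaches its cut-off, she meets the risk criterion regardless.

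**Step 8. Does it reach the design calculation?** The sample size uses a difference of 15.1 − 6.1 = 9.0 points with SDs of 17.7 and 17.1. A t-test calculation gives 59.7, so 60 per arm; 60/0.70 = 85.7, so 86 per arm and 172 in total. The plan's figure reproduces, and glycaemia does not enter it.

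**The case against.** The strongest reply is that this is a slip in a bracketed equivalent that may never have been used. The mg/dL value is printed first. Recruitment is through the oncology unit of one hospital. Nothing in the document shows that screening glucose is reported in mmol/L, that reporting units differ between women, or that anyone applied 6.05. The two HOMA-IR formulas show that either unit can serve in that calculation, not that screening used mmol/L. All of this stands. A reader might infer that eligibility does vary with the laboratory's unit; the document supports only that it could, if the mmol/L value were applied.

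Three further inferences are tempting and not supported:

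- **The eCRF contains the wrong limit.** Data management {19} mentions programmable edits in general terms and shows no glucose limit or unit.
- **A planned analysis by metabolic syndrome is contaminated.** No listed outcome or named analysis uses the syndrome as a category. The nearest text, in the additional analyses {20b}, mentions the metabolic and clinical profile as possible exploratory covariates.
- **The treatment comparison is biased.** Eligibility is settled before randomisation, so a misread cut-off would not act differently in the two arms, and stratification is by anthracycline treatment.

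The reply does not remove the contradiction. The text is intact, no other section corrects it, and it lies in an inclusion criterion, not in background prose.

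**Conclusion.** The point holds in limited form. The glycaemia criterion states two different thresholds, 8.9 mg/dL (0.49 mmol/L) apart by the protocol's own conversion factor. This is certain from the document and needs no outside source.

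The consequence is conditional and probably small. It requires that the mmol/L value was applied and that a woman met all the conditions in step 7 together. The document gives neither the reporting unit nor the share of women in that position, so no count can be offered. The sample size, the primary analysis and the comparison between randomised arms are not affected. Which threshold is clinically intended is for the sponsor to say.

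**What to change.** In Eligibility criteria {10}, reconcile the two figures to one threshold and state which unit governs. If 100 mg/dL is the intended value, its equivalent is 5.56 mmol/L; if 6.05 mmol/L is intended, its equivalent is 108.9 mg/dL. This costs one corrected number and a short clause.

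Confirm which value was used at screening and in any eCRF check. If it was the mg/dL value throughout, and that is the intended one, nothing more is needed. Only if the mmol/L value was actually used, review the records of women, enrolled or refused, whose glycaemia lay between the two values and whose eligibility turned on this factor. That review covers few records and needs no change to the analysis.

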### Who will take informed consent? {26a}

In compliance with Good Clinical Practice (GCP) guidelines, all participants will be informed of the purpose of the research, the possible risks, and their right to withdraw at any time from the study without prejudice and without jeopardy to their future medical care at the center. Each participant will agree to cooperate in all aspects of the study and will give informed written acknowledgment (signed informed consent form [ICF]) to the investigator prior to participation in the study. If necessary, ICF is revised during the study, and active participants will sign the new version in order to continue participating in the study.

### Additional consent provisions for collection and use of participant data and biological specimens {26b}

Additional consent is not necessary as the participants were asked to agree about the use of data and biological specimens for scientific purposes in the original informed consent. Biological specimens are blood, serum, and fecal samples. On the consent form, participants are informed that they have the right to forbid the use of their data and/or biological specimens from the study should they choose to withdraw from the trial.

## Interventions

### Explanation for the choice of comparators {6b}

Leisure-time physical activity is a well-known strategy for the prevention of cancer recurrences [18]. Therefore, for ethical reasons, the nutritional and physical activity counseling will be administered to the control arm, and its effects will be compared to the effects of the supervised MoviS training performed by the intervention arm.

### Intervention description {11a}

Patients will be randomly allocated to the intervention arm (lifestyle recommendations and MoviS Training) or the control arm (lifestyle recommendations). The MoviS training consists of 3 months of aerobic exercise training (2 days/week of directly supervised by an exercise specialist and 1 day/week of remotely supervised exercise) with a progressive increase in exercise intensity (40–70% of heart rate [HR] reserve [HRR]) and duration (20–60 min). Even though several methods can be used to tailor exercise intensity [19], in the present trial, exercise intensity will be prescribed using percentages of HRR corresponding to moderate and vigorous intensity categories as suggested by the current breast cancer-specific guidelines [8, 20]. Each session will start with a 5-min warm-up period, which will be used to gradually reach the target exercise intensity (i.e., HR). Additionally, to account for several physiological adjustments that happen during prolonged aerobic exercises (e.g., cardiovascular drift), heart rate responses will be monitored throughout the training sessions and external exercise intensities (e.g., bike wattage or treadmill speed and grade) will be adjusted to maintain the target HR throughout each training session [21]. Particular focus will be given to participants’ compliance with the prescribed exercise intensity (i.e., target HR) and to their ability to maintain it while training under the direct supervision of an exercise specialist (2 days/week) and autonomously (1 day/week), Indeed, HR monitors will be given to the participants allocated to the intervention arm, who will be instructed on how to use them. Then, the intervention arm participants will be educated on how to independently reach and maintain the desired exercise intensity (i.e., target HR) by means of personalized feedback given by an exercise specialist. During the directly supervised sessions, personalized feedback on how to increase compliance with the desired exercise intensity will be given live, in real-time, based on the HR responses to the exercise, whereas, regarding the remotely supervised sessions performed autonomously by the participants, the feedback will be given after the completion of the training sessions according to the training log, which will include the HR responses to the training session. The directly supervised sessions will be performed in a gym using treadmills or stationary bikes, whereas the remotely supervised sessions will be performed indoors or outdoors according to the possibilities and preferences of each participant. Regardless of the exercise modality, the external exercise intensities (e.g., walking speed and grade or cycling wattage) will be adjusted to reach and maintain the prescribed target HR. Group training sessions and continuous supervision by an exercise specialist, either directly or remotely, will be used as a motivational tool in which adherence will be mainly driven by intrapersonal (e.g., health-related) and interpersonal motives (e.g., empathy with exercise specialists and enjoyment).

Both arms will receive counseling by dieticians on healthy lifestyle habits (nutrition and exercise) based on the World Cancer Research Fund (WCRF) 2018 guidelines through the DIANA-Web platform. The DianaWeb Project is a community-based participatory research that uses a specific interactive website that contributes to the growth of knowledge about lifestyle to be adopted by sharing recipes, movement strategies, and how to manage the change in daily practice involving Italian women with a BC diagnosis [22]. All patients will also undergo psychological well-being counseling by a psychologist, which comprises evaluation for anxiety and depression.

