### Sample size {14}

The sample size was calculated with the aim of verifying the differences between the QoL changes in the two groups (i.e., intervention and control arm), after 3 months of intervention.

The QoL expected improvement in the experimental group at 12 weeks is 15.1 ± 17.7, while in the control arm, it is 6.1 ± 17.1 [24]. Using a *t*-test for independent samples, with an alpha of 0.05 and statistical power of 0.80, to find differences in QoL improvements between the two groups at the end of the intervention, 60 participants per group will be needed. Considering an expected drop-out of 30%, a total of 172 patients will be recruited. The sample size was calculated using Stata statistical software (StataCorp. 2013. Stata Statistical Software: Release 13. College Station, TX: StataCorp LP).

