## Statistical methods

### Statistical methods for primary and secondary outcomes {20a}

A mixed-design ANOVA will be used to compare the changes over time (from T1 to T2, within factor) in the primary outcome between intervention and control arms (between factor). The sample size was calculated to test the hypothesis of no differences between the changes in the primary outcome of the two groups (i.e., interaction effect of the between and within factors of the mixed-design ANOVA). If a significant effect is found, post hoc pairwise comparisons will be used.

Secondary outcomes will be analyzed using repeated measures MANOVA models, with difference-based contrasts.

For all tests, a 2-sided *α* level of significance of 0.05 will be used and, if necessary, the *α* level inflation due to multiple tests will be accounted for by using the appropriate correction (e.g., Bonferroni, false discovery rate, etc.). The statistical test assumptions will be assessed and, if not met, either data transformation or alternative statistical methods (e.g., GEE, non-parametric analyses, etc.) will be performed.

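### Only the exercise arm trains in specialist-led groups, yet the sample size and primary ANOVA treat all women as independent, so the 80% power rests on an unstated assumption of no group effect

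*Protocol article*

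**What the plan says.** All places are in the Protocol article.

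- **Sequence generation {16a}:** women are allocated individually, 1:1, in permuted blocks of four, stratified by anthracycline treatment.
- **Intervention description {11a}:** the exercise arm has two gym sessions a week under an exercise specialist and one session done alone with remote feedback. On delivery it says: "Group training sessions and continuous supervision by an exercise specialist, either directly or remotely, will be used as a motivational tool". It expects adherence to come partly from interpersonal motives, and names rapport with the specialist and enjoyment as examples. Controls receive lifestyle recommendations without this training.
- **Sample size {14}:** "The QoL expected improvement in the experimental group at 12 weeks is 15.1 ± 17.7", "while in the control arm, it is 6.1 ± 17.1". The method is: "Using a *t*-test for independent samples, with an alpha of 0.05 and statistical power of 0.80". The result is that "60 participants per group will be needed", raised to 172 in total for 30% drop-out. No allowance is made for correlation between women.
- **Statistical methods {20a}:** "A mixed-design ANOVA will be used to compare the changes over time (from T1 to T2, within factor) in the primary outcome", with arm as the between factor. No term for training group or specialist appears. "For all tests, a 2-sided *α* level of significance of 0.05 will be used". If assumptions fail, transformation or another method may be used, with GEE as one example.

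**The concern.** Individual randomisation makes women independent at entry. It does not keep them independent once one arm is treated together. Women who share a group, a timetable and a specialist can have correlated changes in quality of life, and here the shared setting is meant to work on motivation. The outcome is self-reported and the participants know their allocation, so such an influence can reach it. This is a partially nested design, with grouping in one arm and none of that kind in the other.

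The within-woman factor of the ANOVA deals correctly with two measurements on the same woman. Nothing in the model deals with women who share a group. If the within-group correlation is positive, the standard error of the arm-by-time interaction is too small. The named test then rejects more often than 5% under the null, and a test that respects the grouping has less than the stated power.

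**Working it through.** **Inputs from {14} and {20a}.** Mean changes 15.1 and 6.1, so the difference is 9.0. SDs of change 17.7 (exercise) and 17.1 (control). 60 evaluable women per arm, two-sided alpha 0.05.

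**Step 1. Reproduce the plan's figure under independence.**
- Variance of the difference = 17.7²/60 + 17.1²/60 = 5.221 + 4.874 = 10.095, so SE = 3.177.
- Noncentrality = 9.0/3.177 = 2.833. With about 118 degrees of freedom, power = 0.802 (0.795 at 59 per arm), so 60 per arm is right.
- 120/0.70 = 171.4, rounded up to 172.

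The plan's arithmetic is correct.

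**Step 2. A plausible group size (assumption).** The protocol gives none. Trial status puts recruitment from January 2020 to the end of May 2023, about 41 months. Twelve weeks is 2.76 months.
- Randomised exercisers in the programme at once: 86/41 × 2.76 = 5.8.
- Evaluable exercisers at once: 60/41 × 2.76 = 4.0.

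The calculation uses 60 evaluable women, so 4 is the matching figure and 6 an upper value. Groups larger than 6 would exceed the average number of women in the programme at once.

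**Step 3. Allow for grouping in the exercise arm only.** With group size m:
- Variance = 17.7² × [1 + (m − 1) × ICC]/60 + 17.1²/60 = v1 + v2.
- Satterthwaite df = (v1 + v2)² / [v1²/(60/m − 1) + v2²/59].
- Power comes from the noncentral t with these df.
- False-positive rate of the unadjusted test ≈ 2 × P(Z > 1.96/r), where r is the true SE divided by the independence SE.

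Example, m = 6 and ICC 0.05: design effect 1 + 5 × 0.05 = 1.25; v1 = 5.221 × 1.25 = 6.527; SE = √(6.527 + 4.874) = 3.376; r = 3.376/3.177 = 1.063; df = 25.3; noncentrality = 2.666; power = 0.727; false-positive rate = 0.065.

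| Group size | ICC | r | df | Power, grouping respected | False-positive rate, unadjusted |
|---|---|---|---|---|---|
| 4 | 0 | 1.000 | 43.4 | 0.791 | 0.050 |
| 4 | 0.01 | 1.008 | 42.6 | 0.784 | 0.052 |
| 4 | 0.05 | 1.038 | 39.7 | 0.759 | 0.059 |
| 6 | 0 | 1.000 | 29.7 | 0.782 | 0.050 |
| 6 | 0.01 | 1.013 | 28.7 | 0.771 | 0.053 |
| 6 | 0.05 | 1.063 | 25.3 | 0.727 | 0.065 |

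Simulating the unadjusted two-sample test on change (100,000 trials per setting) gave false-positive rates of 0.051 (m = 4, ICC 0.01), 0.052 (6, 0.01), 0.058 (4, 0.05) and 0.064 (6, 0.05), in line with the formula.

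**Step 4. Separate correlation from degrees of freedom.** At ICC 0 the nested test already has power 0.791 (m = 4) or 0.782 (m = 6) against 0.802. This cost of 1 to 2 points comes only from estimating a group variance from few groups. At m = 6 and ICC 0.05, keeping 118 df would give 0.753. Of the drop from 0.802 to 0.727, about 5 points are therefore correlation and 2.6 points are degrees of freedom.

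**The case against.** The strongest reply is that no correlation is documented. The protocol gives no ICC, group size, number of groups or number of specialists, and at ICC 0 its figures are exact. A reader might infer that the power and standard error are definitely too favourable, or that the trial is undersized. The document does not support that, because it shows that the independence assumption is open to doubt, not that it is false. At ICC 0.01 the false-positive rate is hardly above 5%.

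A reader might also take 73% as the expected power. That figure needs groups of 6, which comes from counting randomised women, while the calculation uses 60 evaluable women. The matching size of 4 gives 0.76 at ICC 0.05.

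Further points have weight:
- Exercise intensity is set individually by heart rate, feedback is personal, and one of three weekly sessions is done alone. All of this may keep the ICC low.
- Continuous recruitment fits rolling attendance as well as fixed groups. A group effect would then be an approximation.
- Both arms share dietary and psychological counselling, the web platform, group chats and social events, so controls are not perfectly independent either. Those influences are common to the arms, whereas the training groups are not.
- The fallback in {20a} could in principle cover correlation. It is generic, however, and not tied to training groups. A GEE clustered on the woman would leave the matter untouched.

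A separate analysis plan may exist. But the protocol itself fixes the test behind the sample size and the primary model, and both assume independence. These replies limit the size and certainty of the point without removing it.

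**Conclusion.** The point holds as a conditional one. The 80% power and the standard error of the primary ANOVA are valid only if there is no training-group or specialist effect, and the protocol's own account of how the exercise arm is motivated makes that assumption worth stating and checking. Assuming groups of 4 to 6 and ICC 0.01 to 0.05, power falls from 0.80 to about 0.78 to 0.73, and the unadjusted test's false-positive rate is about 0.05 to 0.065. Some of the power loss is the price of the nested analysis. The sample-size arithmetic is not in error. The documents do not compel replacing the primary model, but they do justify a pre-specified sensitivity analysis.

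**What to change.** 1. **Record the grouping.** Add one eCRF field for each exerciser's training group or main supervising specialist. Trial status says data collection is continuing, so this can still be captured. If membership rolls, record the predominant group.
2. **Pre-specify the analysis**, at least as a sensitivity analysis of the same T1 to T2 arm-by-time contrast. Use a partially nested mixed model with a random training-group effect in the exercise arm only, separate residual variances by arm, and Satterthwaite or Kenward-Roger degrees of freedom.
3. **Qualify {14}.** State that 80% power assumes no within-group correlation, and show power over a range of ICC and group size, as in the table above.

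The cost is one data field, a few sentences and a less favourable power statement. The interval in that analysis will be somewhat wider, with fewer degrees of freedom. With rolling membership the predominant group is only an approximation. The recruitment target of 172 need not change.
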